## Abstract

**Background:**

Placebo effects are mediated by expectancy, which is highly influenced by psychosocial factors of a treatment context. These factors are difficult to standardize. Furthermore, dedicated placebo research often necessitates single-blind deceptive designs where biases are easily introduced. We propose a study protocol employing a virtual experimenter – a computer program designed to deliver treatment and instructions – for the purpose of standardization and reduction of biases when investigating placebo effects.

**Methods:**

To evaluate the virtual experimenter’s efficacy in inducing placebo effects via expectancy manipulation, we suggest a partially blinded, deceptive design with a baseline/retest pain protocol (hand immersions in hot water bath). Between immersions, participants will receive an (actually inert) medication. Instructions pertaining to the medication will be delivered by one of three metaphors: The virtual experimenter, a human experimenter, and an audio/text presentation (predictor “Metaphor”). The second predictor includes falsely informing participants that the medication is an effective pain killer, or correctly informing them that it is, in fact, inert (predictor “Instruction”). Analysis will be performed with hierarchical linear modelling, with a sample size of *N* = 50. Results from two pilot studies are presented that indicate the viability of the pain protocol (*N* = 33), and of the virtual experimenter software and placebo manipulation (*N* = 48).

**Discussion:**

It will be challenging to establish full comparability between all metaphors used for instruction delivery, and to account for participant differences in acceptance of their virtual interaction partner. Once established, the presence of placebo effects would suggest that the virtual experimenter exhibits sufficient cues to be perceived as a social agent. He could consequently provide a convenient platform to investigate effects of experimenter behavior, or other experimenter characteristics, e.g., sex, age, race/ethnicity or professional status. More general applications are possible, for example in psychological research such as bias research, or virtual reality research. Potential applications also exist for standardizing clinical research by documenting and communicating instructions used in clinical trials.

## Background

To a large extent, placebo effects arise from the psychosocial setting in which a treatment is delivered, most notably the physician/patient or experimenter/participant interaction [1]. These effects can be substantial [2, 3]. However, it is difficult to systematically tease apart the contributions made by separate aspects of an interaction. In this paper, we propose the use of a virtual experimenter as a platform to address these issues with minimized risk of bias.

We define the placebo effect (PE) as that part of an actually experienced symptom improvement mediated by psychological expectancy concerning a treatment, regardless of the treatment’s actual efficacy [4]. This expectancy arises from multiple sources in the treatment’s psychosocial context, such as verbal instruction [5], conditioning [6] or social learning [7].

PEs are most well known in the context of randomized clinical trials, where the placebo group receives an inert treatment to serve as control for the actual treatment [8]. However, the change happening in the placebo group is always a composite measure, including the actual placebo effect and numerous other factors [9, 10]. Some of these are a feature of the nosological subject matter, such as the natural course of disease and the fact that people tend to seek out treatment at peaks of symptom severity. These factors can lead to regression to the mean, which describes the fact that extreme values will tend to converge toward less extreme values at retest. Other factors include distinct psychological phenomena, like response biases, which cause study participants to modify their answering behavior after receiving a placebo treatment, without actually affecting their symptom experience [9, 10].

To investigate PEs per se, dedicated research involving additional control groups has been performed. Different from classical clinical trials where the placebo group is the control group, dedicated placebo research inquires into the conditions in which PEs occur, and the mechanisms involved [11]. A number of paradigms exist which employ active treatments [11, 12]. For example, in the “balanced placebo design” [13], the actual treatment (active vs. inert) is paired with the information with which it is administered (“active” vs. “inert”). Like double-blind clinical trials, this permits blinding. However, use of active treatment is often precluded due to ethical and regulatory obstacles. Especially when investigating healthy participants to identify basal mechanisms of the placebo response, this frequently leads to the employment of more basic designs. One of these designs is a single-blind deceptive placebo design. For example, in one of our own studies [14], two groups receiving the same inert treatment were compared, with one of them being (deceptively) told that the treatment is actually effective, and one being (truthfully) told that it is not. Under these circumstances, the above mentioned psychological confounds can be exacerbated. Not only are the investigated variables highly affected by psychological influences to begin with, but additionally, blinding of the experimenter is frequently impossible or impractical [10]. Consequently, while great progress has been made in identifying the neuropharmacological [15], neuronal [16] and even genetic [17] underpinnings of placebo responsiveness, some of this research stands on shaky foundations [10]. If the experimental interaction is not tightly controlled, it is difficult if not impossible to establish causation in placebo trials: The reported symptom change of a participant cannot merely be attributed to the (intentional) treatment difference, but possibly to subtle but systematic (unintentional) differences in the broader experimental context. These differences contribute to a mean difference of experimental group versus control group. Some of these context factors have been explored, such as experimenter variables like a reassuring, positive attitude [18], empathy [1], affect-oriented communication [19], professional status [20] or sex [21]. However, these studies have been rarely replicated.

We propose that some of the limitations of research addressing psychological entities like symptom experiences could be overcome by the use of a virtual experimenter (VEx; Fig. 1). The VEx is a computer program designed to perform the function of randomized treatment allocation and treatment delivery. While preserving or even exceeding psychosocial characteristics of a conversation [22] (which are required for PEs to arise in the first place), it would perform social tasks with complete standardization – this is in contrast to pre-recorded messages, which do not induce the same extent of social presence as an embodied conversational agent.

**Fig. 1 Fig1:**
[figure not shown]
“[name]”, the virtual experimenter

From this framework, it is easy to manipulate aspects of the instruction or the appearance of the VEx without changing any of the other parameters, as would almost necessarily be the case if the task were performed by a human experimenter (HEx). While virtual reality has been used in some related applications before (e.g., as “virtual reality-based analgesic” distraction techniques [23] or interview partners [24] in the scope of psychological research), its use for the proposed purpose has not been investigated.

In the following, we present a comprehensive study protocol to test the VEx’ efficacy in eliciting PEs, to establish its viability as a substitute for treatment allocation and delivery by a HEx (section “Methods”). Due to the well-documented efficacy of placebo on pain (placebo analgesia), a pain modality will be employed as the method for symptom induction. The protocol combines several features (virtual reality software and pain protocol). These components have been separately investigated in pilot studies presented following the proposed protocol (section “Current status”). We outline the creation of the VEx under “Development of the stimulus material”, and its evaluation under “Pilot study 1”. To assess reproducibility and possible carry-over effects, we conducted a pilot study of the pain protocol, as well. Core findings are presented under “Pilot study 2”.

## Methods

We propose the following methods to determine the VEx’ efficacy in inducing PEs. The interaction with the VEx will be compared to an HEx interaction, and an audio/text based interaction. All non-interventional interactions such as the pain testing will be performed by a blinded laboratory assistant.

### Design

The study will follow a partially blinded, deceptive, repeated measures design. Participants will undergo a baseline pain measurement (five 60 s immersions of the hand in hot water; see “Pain protocol”), followed by treatment with a supposed pain killer, and a retest pain measurement. In this design, every participant will only receive an oral placebo (no active medication), but groups will differ as to the instruction about the (actually inert) “medication’s” efficacy.

Within-persons and between-persons predictors include■ the mode of treatment/instruction presentation (between-persons predictor Metaphor, 3 levels: HEx, VEx, text/audio)■ the instruction itself (between-persons predictor Instruction, 2 levels: “medication” (deceptive) vs. “inert” (truthful)); this manipulation is double-blind to both participant and laboratory assistant■ the pain measurement repetition, which constitutes nested within-persons predictors (immersion Time nested in immersion Trials nested in immersion Sequences). In the scope of this study outline, we will only address Trials and Sequences pertaining to the expected results.

See Fig. 2a for a design and protocol outline. Within-persons and between-persons predictors correspond to level 1 and level 2 variables used in hierarchical linear modelling nomenclature (see “Analysis and sample size estimation”).

**Fig. 2 Fig2:**
[figure not shown]
Experimental design (A) and participant verbal input during the interaction (B). **a** Between pain baseline and retest, participants will be randomly assigned to Metaphor and Instruction. Different sections of the participant interaction with Metaphor (*Introduction* through *Farewell and wrap up*) are displayed. The shaded area (*Condition assignment*) corresponds to allocation to Instruction. **b** Corresponding to the participant interaction sections, the arrows indicate the time points of verbal input required for the instructions to proceed

### Study population

Participants will be recruited from Clemson University's student population, staff and faculty. Exclusion criteria will be applied (Table 1). We will balance the sample for sex/gender and will attempt mean matching for age, to yield roughly equal distributions in all combinations of the two between-persons predictors. Both sex/gender and age are possible confounds, as they may influence pain sensitivity [25, 26], placebo responsiveness [27] or the reception of the technology involved in the intervention [28].

**Table 1 Tab1:** Inclusion criteria for the proposed study

18 < Age < 64	
No past or present brain or nerve conditions (e.g. fainting, stroke, neuropathy)	
No past or present pain disorder (e.g. diagnosed migraine, chronic back pain)	
No open wounds or skin conditions on the dominant hand (e.g. hangnail, graze)	
Abstained from recreational drugs (alcohol, cannabis) for at least 24 h before the lab visit	
Abstained from pain medication (and other medication feasibly affecting experimental parameters) for at least 24 h before the lab visit	

Due to the deceptive nature of the protocol, full informed consent cannot be procured prior to participation; instead, a cover story will be presented to the participants. After the experiment, participants will receive full disclosure of the manipulation. Express permission will be asked of them to consider their data in the analysis. They will be given the choice to withdraw their data from analysis at any point prior to publication, without the need for justification.

### Procedure

Participants will continually rate their pain during Sequence 1 under supervision of a laboratory assistant. They will then be randomly assigned to one of the 3(Metaphor)*x*2(Instruction) experimental groups. In a separate room, they will interact with the Metaphors delivering the Instructions. For the VEx and audio/text condition, interactional components are displayed in Fig. 2b. Crucially, neither assignment will be revealed to the laboratory assistant.

During the placebo manipulation, the inert medication will be automatically dispensed using a self-constructed pill dispenser controlled by an Arduino platform (https://www.arduino.cc/). For VEx and audio/text condition, pill dispension will be performed by the presentation software; in the HEx condition by pressing a button.

An overall inter-Sequence interval of 35 min will be observed for cutaneous sensitivity to recover, and to provide a plausible cover story for the medication to take effect (in the “medication” instruction).

The pain change at retest, compared between experimental groups, will be the main outcome.

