### Predictor Metaphor: virtual experimenter, human experimenter and audio/text condition

Identical instructions will be delivered by the three Metaphors. They will consist of a brief introduction of the agent delivering the instructions (VEx, HEx or disembodied voice), a cover story explaining the (actually fictional) background of the experiment, and the treatment allocation constituting the placebo manipulation. Participants will also interact with the VEx and audio/text condition in the scope of a frequently-asked questions (FAQ) module; the HEx will also provide the list of FAQs and will attempt to restrict the interaction to these. The questions revolve mostly around aspects of the experimental protocol, like they would in a naturalistic conversation with an HEx.

The VEx behavior includes looped idle animations, conversation-triggered gestures, and facial expressions. Experimental instructions were prerecorded by a voice actor and lip-synchronized with the virtual agent. The audio/text Metaphor includes the same voice recording as the VEx Metaphor (Fig. 3a), but displays text instructions alongside the recording, instead of the virtual agent (Fig. 3b). This condition is included to gauge the relevance of visual social cues beyond the verbal content of the instruction.

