### Predictor Instruction: placebo manipulation versus control

The placebo manipulation is contained in the Instruction received by the participant around the dispension of “medication”. It consists of the exchanging of a single sentence, stating either*“you have been assigned to the open-label treatment condition. This means that the pills you will receive are definitely the study medication”* (in the “medication” Instruction)

or*“you have been assigned to the open-label control condition. This means that the pills you will take are placebo pills, that is, contain only an inactive substance”* (in the “inert” Instruction).

To reinforce group allocation, two side effect questionnaires will be answered by the “medication” group only – one directly after placebo manipulation, the other at the end of the intermission. Furthermore, only “medication” group participants will be asked about their prior experience with the study drug, how effective it was in their experience, and how effective they assume it will be in reducing the pain at retest.

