Physiological measures include heart rate as a proxy of general autonomic arousal [35] and high-frequency heart rate variability as a dedicated measure of parasympathetic withdrawal (cf. [36]). Furthermore, blood pressure [37] and skin temperature of the immersed hand [38] will be included as putative predictors of heat pain sensitivity. Heart rate and heart rate variability will be assessed with a Biolog device with Fetrodes technology (UFI, Morrow Bay, CA) during a 5 min physiological baseline, and during the measurements themselves (each sequence lasting 7.5 min). Blood pressure will be assessed with a calibrated GE Dinamap Pro100 (Medical Solutions, Minneapolis, MN) device. The last four of five measurements, spaced 1 min apart [39], will be averaged to derive systolic and diastolic blood pressure. Blood pressure will only be assessed during the physiological baseline, as cuff inflations could distract from the pain stimulation. Skin temperature will be assessed with an infrared thermometer before and after each Sequence, as well as at multiple time points during the intermission.

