### Bias reduction and manipulation check

A manipulation check will be performed assessing any doubts or suspicions concerning the treatment allocation or the cover story. Preliminary data indicates that the cover story, including the group allocation, are considered convincing by the participants: 18 of 19 people answered “no” to a post-experimental question asking “Did you at any point find the experimental instructions unconvincing?”.

Allocation to the experimental groups will happen in a room adjacent to the room where the pain measurement takes place, and without insight of the laboratory assistant into the allocation. He or she will therefore be fully blinded to the treatment allocation when performing the retest. Measures will be taken to ensure that allocation is not revealed by the participant: The participant will be asked by the VEx, HEx or audio/text display not to notify the laboratory assistant of their treatment allocation, and the laboratory assistant will document any deviations. Audiovisual recording of the participant/laboratory assistant-interaction will be considered if necessary.

All measurements (except blood pressure and skin temperature) and pain reports will be performed on a computer without communication with the laboratory assistant. Furthermore, the instructions for the continuous pain ratings contain a line to emphasize participant anonymity and non-involvement of the laboratory assistant in data analysis, “This next part is very important: Your ratings will be analyzed by a blinded experimenter only after the session is over. Focus as much as possible on the sensation in your immersed hand, and feel totally free to rate your pain precisely and truthfully. Try not to let my presence or any other thought affect the way you report the sensation, or affect the number of trials you complete.” Also, during the pain measurement, the laboratory assistant will remove himself or herself from the immediate vicinity of the participant to sit down at a table in the participant's field of view, but facing in the same direction as the participant as to not give the participant the feeling of being observed (beyond an initial making sure that all instructions are complied with).

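### The safeguards described do not fully secure the promise that neither Metaphor nor Instruction is revealed to the laboratory assistant

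*Protocol article*

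**What the plan says.** Procedure describes random assignment to six groups (three Metaphors by two Instructions) and promises concealment of both factors: "Crucially, neither assignment will be revealed to the laboratory assistant". Design attaches the double-blind label to Instruction alone: "this manipulation is double-blind to both participant and laboratory assistant".

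Bias reduction and manipulation check gives the safeguards. Allocation takes place in an adjacent room, out of the assistant's knowledge, and the article concludes: "He or she will therefore be fully blinded to the treatment allocation when performing the retest". Each Metaphor also asks the participant "not to notify the laboratory assistant of their treatment allocation, and the laboratory assistant will document any deviations". Audiovisual recording is an option, not a commitment.

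Two other sections bear on the intermission. Under Predictor Instruction, only the medication arm fills in two side effect questionnaires, "one directly after placebo manipulation, the other at the end of the intermission". Under Secondary measures, skin temperature is read before and after each Sequence, "as well as at multiple time points during the intermission".

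**The concern.** The promise covers two assignments, while the request to participants names one thing. A participant who has just been instructed by a virtual figure could mention it to the assistant without breaching the request as described. Metaphor is the factor the study exists to test, so its concealment deserves the same protection as that of Instruction.

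For Instruction, the measures concern the moment of allocation and what the participant says afterwards. They do not address a procedure that differs between arms after allocation and shortly before the retest.

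The main outcome is pain change at retest, compared between groups. The assistant runs that retest, checks at the start that instructions are followed, and remains where the participant can see him or her. The Background argues that small systematic differences in context can produce group differences in deceptive designs. Potential and outlook names unblinding and guessing of allocation as sources of experimenter bias. By the article's own reasoning, the assistant's blinding is a main protection for the comparison.

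**Working it through.** No arithmetic underlies the point, and the plan gives no figure to reproduce. The check compares sections of the protocol article.

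**Step 1: scope of the promise against scope of the request.**
- Promise (Procedure): both Metaphor and Instruction.
- Request (Bias reduction): "not to notify the laboratory assistant of their treatment allocation".
- Meaning of the term (Predictor Metaphor): among the components each Metaphor delivers is "the treatment allocation constituting the placebo manipulation". That is Instruction. The introduction of the agent is listed there as a separate component.
- Result: on the article's own usage, the request covers Instruction. For Metaphor, what remains is the separate room and the assistant not being told. Those hide the interaction but do not restrain a later remark.

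**Step 2: who meets the participant during the intermission.**
- The opening of Methods gives all non-interventional interactions to the blinded assistant.
- Secondary measures schedules temperature readings within the 35-minute interval, and one before Sequence 2.
- Bias reduction exempts skin temperature, with blood pressure, from the rule that measurements are made by computer without communicating with the assistant.
- Analysis and sample size estimation says temperature is written on a score sheet.
- Result: the natural inference is that the assistant takes these readings in person. The article does not say so outright.

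**Step 3: what differs between groups in that interval.**
- By Instruction: the second side effect questionnaire, medication arm only, at the end of the intermission. The inert arm has no stated counterpart.
- By Metaphor: no intermission procedure is described as differing.
- Result: there is one procedural cue, and it concerns Instruction. The route for Metaphor is disclosure by the participant.

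**Step 4: can the assistant see the cue?**
- The questionnaire falls under the computer rule, so its answers are not communicated to the assistant.
- The rule does not say whether the assistant can see that a questionnaire is being completed, or where this happens.
- Result: a possible cue, neither confirmed nor excluded.

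**The case against.** The strongest reply has four parts.

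**The term may be broader.** The paragraph on blinding opens with allocation to the experimental groups, which could mean all six cells. The request would then arguably cover Metaphor. If the term is narrow, the claim of full blinding at retest is equally narrow and agrees with the label in Design. This stands as far as it goes: full blinding at retest should not be read as a claim about Metaphor. The Procedure sentence still covers both assignments, and a participant told to withhold a treatment allocation need not take that to include who spoke.

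**There is more than a separate room.** A reader might infer that blinding is deduced from the room alone. It is not: the article adds that the assistant has no insight into allocation, the request to participants, logging of deviations and possible recording.

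**The questionnaire may give nothing away.** It is computer-based, and both arms complete other state questionnaires during the visit, so being at a survey screen need not mark an arm. Room layout is detail that an article may leave to the full protocol. This reduces the cue to a possibility. It does not remove the asymmetry between arms, which the article states itself.

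**The route to the outcome is narrow.** Immersion prompts are automated, pain is self-rated on a touch screen, the assistant moves away and faces the same way as the participant, and the rating instructions ask participants to disregard the assistant's presence. These measures limit any bias but do not make knowledge of allocation harmless.

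**Conclusion.** The point holds as a gap in protection: the concealment promised for both assignments is not fully secured by the measures listed. For Metaphor, the request to participants does not clearly apply. For Instruction, a task given to one arm only, close to the retest, is a possible cue that the bias section does not address.

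A reader might go further and infer that blinding fails, that intermission procedures reveal both assignments, or that Instruction could be identified in every session. The documents support none of these. No intermission procedure differs by Metaphor, and nothing says the assistant sees the questionnaire.

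The size of any bias cannot be derived from the article, and its direction is not established, least of all for the Metaphor contrast. The conclusion rests on two readings: that treatment allocation means Instruction, as under Predictor Metaphor, and that the assistant takes the intermission temperatures. If the full script already covers the mode of delivery and the questionnaire is completed out of the assistant's sight, a sentence saying so would close the point. Otherwise, the changes should be made before recruitment.

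**What to change.** 1. Extend the scripted request, identically in all three Metaphors, to cover who or what delivered the instructions. Have the assistant log disclosures of Metaphor and of Instruction separately.
2. Give the inert arm a neutral computer survey block of equal length at the same two time points as the medication-only questionnaires. Both arms complete it away from contact with the assistant.

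The cost is one added script sentence and a short extra survey block, with no additional staff or participants.

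A guess of allocation by the assistant is optional. If collected, take it after the retest and report it descriptively. A guess before Sequence 2 would prompt the assistant to think about allocation just before the outcome is measured. Correctly guessed sessions should not be excluded, because that selects on a variable arising after randomisation. If guesses were random, about 1/2 would be right for Instruction and 1/3 for Metaphor. With N = 50 that is 50 × 1/2 = 25 and 50 × 1/3 ≈ 17 sessions, lost without any unblinding having occurred.
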